## Materials and methods

### Experimental design

Adolescent girls with a confirmed diagnosis of mild (Cobb angle ranging from 10° to 20°, no spine surgery) and moderate (Cobb angle ranging from 21° to 35°, no spine surgery) scoliosis (AIS) will be enrolled at the Adolescence Spine Diseases Diagnostic and Therapeutic Center of the Padova University Hospital. Subjects matched in sex and age without AIS—controls (CTRL)—will be recruited through flyers posted in middle and high schools in Padova.

Adolescent girls with AIS and controls will undergo a three-phase experimental protocol (T0, T1, T2).

This longitudinal study aims to follow and quantify alteration in body representation in parallel to the progression of scoliosis from the time of the first diagnosis by the physiatrist (T0) and up to one year after diagnosis (T1, T2). At T0, subjects (AIS and CTRL) will undergo two tasks aimed at investigating possible alterations in *body schema* representation. During the experiment, we will use EEG to record changes in brain oscillations; sEMG to assess possible imbalances in muscle activation, IMUs, motion capture, and force platforms to monitor the performance and movement characteristics during the balance and motor tasks. A self-reported questionnaire and a computer-based test will be administered to all subjects to investigate *body image* alterations in AIS.

After this evaluation (T0), if the adolescent shows low-grade scoliosis, an expert physiotherapist gives her corrective postural exercises to perform daily (30 min / day) until growth is complete. Participants’ performance in scoliosis-specific exercise will be monitored by the physiotherapist at least once a week. The set of exercises is believed to improve postural awareness, proprioception, and ability to dissociate the movements of the lumbar spine from the thoracic one in the different planes of space. Treatment will be planned in the individual patient, based on the dysfunction detected in the clinical assessment. When scoliosis exceeds the 20°Cobb and there is evidence of progression risk, a rigid partial (18 hours/day) or full-time brace (23 hours/day) is also prescribed.

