### Procedure

All methods will be carried out in accordance with the guidelines of the 2008 Helsinki Declaration. Ethical approval has been obtained on April 2023. Written informed consent will be provided by both subjects and their legal guardians.

We estimate recruiting 40 subjects. Considering a 20% dropout (approximately 8 subjects), we expect to acquire data from 30 subjects (15 subjects with AIS and 15 CTRL). For the calculation, we used the average effect size observed in [3] (i.e., the minimum difference between CTRL and AIS subjects for the EEG laterality index in sensorimotor areas) considering error probability (*α*) of 5%, with a power (1 –*β* error probability) of 80%. Power statistical analyses will be repeated after having recorded data at T0 as an additional tool to review the required sample size. If necessary, the sample size will be enlarged.

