To reveal possible alterations in body image representation in adolescent girls with AIS, BUT sub-scores will be calculated (scoring instructions are reported in S1 Appendix). Response accuracy (i.e., percentage number of correct responses over the total number of trials) and reaction times (RTs), collected as outcome variables during the Computerized body self-recognition task, trials will be clustered according to the target stimulus and subsequently analysed. The correlations between the BUT questionnaire subscores and RTs and accuracy will be assessed using the Pearson’s correlation coefficient (r).

The results of AIS-adolescent girls and controls of the same age and sex will be compared by statistical analyses. Shapiro-Wilk normality test will be applied on all the data collected to check the normal distribution. A two-tailed paired sample t-test or a two-sided Wilcoxon rank sum test (*p* < 0.05) will identify differences between the two groups (AIS vs. CTRL) and between the three time points evaluation (T1, T0 and T2) after having run a global test (either repeated measure ANOVA, or Friedman test depending on data normality).

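### The named alternatives, a paired t-test or a rank-sum test, are not counterparts, so one of the two is wrong for AIS vs CTRL and the other for the visits

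*Protocol article*

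**What the plan says.** In the Protocol article, the last paragraph of Foreseen data processing sets out the tests. First, "Shapiro-Wilk normality test will be applied on all the data collected". Then "A two-tailed paired sample t-test or a two-sided Wilcoxon rank sum test", each at p < 0.05, "will identify differences between the two groups (AIS vs. CTRL) and between the three time points evaluation (T1, T0 and T2"), after a global test that is "either repeated measure ANOVA, or Friedman test depending on data normality". The sentence does not assign one test to groups and the other to visits.

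On the control group, Experimental design speaks of "Subjects matched in sex and age without AIS" and says that controls "will be recruited through flyers posted in middle and high schools in Padova". Selection criteria asks for at least 15 girls in each group. Under Procedure, "We estimate recruiting 40 subjects" is followed by an allowance of 20% dropout and "we expect to acquire data from 30 subjects (15 subjects with AIS and 15 CTRL"). The sample may be enlarged after T0. No section describes forming or keeping individual AIS–control pairs.

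**The concern.** A paired t-test has the signed-rank test as its non-parametric counterpart, and a rank-sum test has the unpaired t-test as its parametric one. The plan joins one member of each family and applies the result to two comparisons of different structure. AIS and CTRL are different girls. T0, T1 and T2 are the same girls measured again.

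If normality decides, normal group data go to a paired test without defined pairs, and non-normal visit data go to a test that treats repeated measurements as independent. The first lets an arbitrary ordering of girls affect the p-value of the contrast on which the sample size rests. The second weakens the pairwise assessment of change under treatment, which is part of the stated aim. Several planned outcomes are bounded or non-negative (reaction times, percentage accuracy, Euclidean error, sway path, ellipse area), so the non-normal branch may well be used.

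**Working it through.** **1. The plan's own figure.** Procedure gives 15 per group, alpha 5% and power 80%, but no numerical effect size, so the sample size cannot be reproduced forwards. Solved backwards for a two-sided unpaired t-test with 15 per group, it corresponds to d = 1.06. That value is used below as the design effect.

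**2. Test against data structure.**

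| Comparison | If normal, the plan gives | If non-normal, the plan gives |
|---|---|---|
| AIS vs CTRL, no pairs | paired t-test: does not fit | rank-sum: fits |
| Visits, same girls | paired t-test: fits | rank-sum: does not fit |

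If true 1:1 pairs existed, the paired t-test would fit in both rows and rank-sum would ignore the pairing in both.

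**3. AIS vs CTRL: paired t-test on unpaired groups.** With no within-pair correlation, both tests have noncentrality d·√(n/2) = 1.06 × √7.5 = 2.90. They differ in degrees of freedom:
- Unpaired: 28 df, critical value 2.048, power 80.0%.
- Arbitrarily paired: 14 df, critical value 2.145, power 77.0% (77.1% in simulation).

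Simulated type I error is 5.0% for both. In 500 simulated trials at d = 1.06, each re-paired at random 100 times, 34% had a verdict that depended on the pairing (between 1% and 99% of pairings significant). Under a stricter criterion, 5% to 95%, the share is 28%. A paired test also needs equal numbers. Losing 20% of 40 leaves 40 × 0.8 = 32 girls, and nothing ensures a 16/16 split.

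**4. Visits: rank-sum on repeated measurements.** The documents give no between-visit correlation r, so the values here are assumptions. For a difference between two visits, the variance is 2σ²(1 − r). An unpaired test works as if it were 2σ², which overstates the standard error by 1/√(1 − r): 1.41 at r = 0.5, 1.83 at 0.7 and 2.24 at 0.8. The test is therefore conservative. Its simulated type I error with normal data, n = 15, is 0.8% at r = 0.5 and 0.1% at r = 0.7.

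The procedure as read was simulated with n = 15 and a shift of 0.6 SD (on the log scale for log-normal data). It applies a paired t-test if both visits pass Shapiro-Wilk at 0.05, and otherwise rank-sum. The comparator has signed-rank in the non-normal branch.

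| Data | r | As planned | With signed-rank | Loss (points) |
|---|---|---|---|---|
| Log-normal | 0.5 | 29% | 50% | 21 |
| Log-normal | 0.7 | 27% | 70% | 43 |
| Log-normal | 0.8 | 27% | 85% | 58 |
| Normal | 0.5 | 55% | 58% | 3 |
| Normal | 0.7 | 75% | 79% | 4 |
| Normal | 0.8 | 87% | 92% | 5 |

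Normal features lose little because most of them reach the paired t-test, which is right for visits. At low correlation the loss is also small for skewed data. With the effect set so that a paired t-test on normal data has 80% power, the log-normal figures at r = 0.3 are 66% for rank-sum and 72% for signed-rank.

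**The case against.** The strongest defence is that the wording is loose but the intention sound: a paired t-test meant for visits and rank-sum for groups, or rank-sum written where signed-rank was meant. The text supports neither. It has no "respectively", it names the groups first and the paired test first, and it ties the choice to normality. The first reading would also leave no non-parametric test for visits, so a significant Friedman test would be followed by a paired t-test. The second would leave the groups with paired tests only.

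A second defence is that matching on age and sex, with 15 and 15 expected, could mean 1:1 pairs. The documents neither state nor exclude this, and recruitment by flyer does not prevent it. With true pairs, the paired t-test is valid and stronger (89% against 84% at a within-pair correlation of 0.3). That part stands, but the rank-sum alternative would then ignore the pairing.

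A third point also stands: the global tests, repeated-measures ANOVA and Friedman, respect the within-girl structure over visits. The fault over visits is confined to the pairwise follow-up.

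A reader might infer that the group results are unsound. The figures do not support that: type I error stays at 5.0% and the power cost is about 3 points. A reader might also infer that most power to see change is lost throughout. That does not hold for normal features. For non-normal ones, a loss of more than half needs a correlation of roughly 0.6 or more, which the documents do not provide.

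**Conclusion.** The rule is wrong as written, and no reading makes the whole sentence right. Its consequences are limited.

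- **AIS vs CTRL:** the result is undefined until pairs are defined, and unequal groups cannot be used in full. False positives do not increase. The power figures assume d = 1.06, 15 per group and no within-pair correlation.
- **Visits:** the loss falls on pairwise comparisons of features that fail Shapiro-Wilk. It is 21 to 58 points in the log-normal example for assumed correlations of 0.5 to 0.8, and less at lower correlations. For normal features it is 3 to 5 points. The error is towards missing a change, so a null follow-up result on a skewed outcome could be mistaken for absence of change.

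The sizes over visits rest on assumed correlations, a 0.6 SD shift, 15 girls and the log-normal shape. The mismatch of tests rests on none of these.

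**What to change.** Replace the sentence with one that assigns tests by data structure first and by distribution second:

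- AIS vs CTRL at a given visit: unpaired t-test (for example Welch) or Wilcoxon rank-sum test.
- Visits within a group, after the global test: paired t-test or Wilcoxon signed-rank test.
- If 1:1 age-matched pairs are formed and kept, state how they are formed and what happens when one member drops out, and use the paired t-test or signed-rank test for AIS vs CTRL as well.

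The cost is one sentence of analysis wording, with no extra data, visits or participants.

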Parallel to the study of CNS response through non-invasive brain imaging techniques in AIS, human motion analysis provides insight on the quality of balance and movement. Marker-based stereophotogrammetry, inertial measurement sensors, surface electromyography (sEMG) sensors, and force plates, among other systems, can provide valuable information on joint kinematics, muscle activation, center of mass (COM), and center of pressure (COP) displacement. Balance control measured through force plates revealed no differences between girls with AIS and CTRL in a standing upright position [3, 14, 16, 17]. Differences between girls with AIS and CTRL have been detected when the experimenters asked the participants to stand upright while either raising their arms with eyes closed or during sensory cues alteration (i.e., ankle tendon vibration or galvanic vestibular stimulation) [3, 14, 16].

Quantifying EEG, sEMG and motion patterns before, during and after bracing and physiotherapy treatment could be a first step to clarify what triggers the lateral spinal curvature that produces asymmetric loading of the skeletally immature spine, which, in turn, causes asymmetric growth and a progressive wedging deformity [18].

Last but not least, body representation alterations, i.e., alterations in both the *body schema* and the *body image*, need to be better understood in this clinical population. *Body schema* refers to the position and configuration of the human body as a 3-dimensional object in space. The body schema is the sensorimotor representation of the body used to plan and execute movements [9, 19–21]. Alterations of body schema have been proposed to parallel the development of spinal deformity in AIS [8]. *Body image* is a complex psychological construct that encompasses different dimensions, namely perception, cognition, affect, and behavior [22]. Body image refers to the disfiguring appearance caused by scoliosis spinal deformities, and the related brace treatments. Altered body image has a notable impact on the mental health of adolescents [23], which has detrimental effects both on quality of life and adherence to treatment [24, 25].

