The same physical, neurological, and cognitive evaluations of T0 will be repeated after 6 (T1) and 12 months (T2) of therapy in AIS and after 12 months (T2) in CTRL. A team of bioengineers, physiatrists and physiotherapists will perform the experimental protocol to ensure the comfort of the subjects and the quality of the data (Fig 1).

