Body schema refers to the sensorimotor body representation that entails tracking and updating the position and configuration of both body parts and other objects in space towards which reaching movements can be planned [27]. The functional representation of the action space immediately surrounding the body, also known as the peripersonal space, usually undergoes changes concurrent with body schema alterations. Through the target reaching we will assess if possible body schema alterations in adolescent girls with AIS can alter the planning of the movement within the peripersonal space. The forearm bisection task is a simple and common test widely used in clinical and research fields to investigate the body schema [27]. We will use this task to test whether adolescent girls with AIS have a different representation of the metric properties of their own body compared to CTRL. By replicating the same tasks at time T1 and T2, we will test how the body schema will change as a function of control postural exercises or the effectiveness of brace therapy. The first test of the body schema (T0) is expected to highlight a possible alteration in the perception of the shoulders-waist proportion and in the inclination of the trunk. We expect a decrease in alteration in their body representation due to the treatment. The two tasks are designed to reveal body schema alterations at T0 in the AIS group, which should improve significantly after the 6 month exercise and brace-treatment period (T1).

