Cognitive and behavioral assessment will investigate two aspects of body image perception: how subjects perceive their body appearance and the emotional and cognitive aspects of body [26]. We expect to find significant differences between the AIS group compared to CTRL at T0, with AIS having a worse self-attitude towards body image (i.e. body image dissatisfaction). Worst score in the sub-domains of global severity index, body image concerns, avoidance and compulsive self-behaviors (BUT-A), and specific higher concerns for shoulders, chest, and hips than other body parts (BUT-B). Second, we expect to find body attentional bias in the AIS group towards disease-specific body parts (shoulders, back), meaning faster reaction time and higher accuracy in response to disease-relevant images, and particularly to own body-relevant images. At T1, we expect to find a significant improvement in self-attitude scores for body image compared to T0 and a reduction of the attentional bias towards disease-relevant body parts, which means no differences in reaction time and accuracy between relevant and irrelevant body parts.

A risk of the proposed experimental protocol is boredom and loss of interest and compliance due to its duration (circa 80 min) and complexity. If necessary, the protocol can be divided into three separate sessions on three different days. Block (i), blocks (iii-iv), and block (v) of the protocol are independent and investigate different research questions. Another possible risk is related to the longitudinal design. Adolescent girls with AIS may not be available to repeat neurophysiological, postural, and cognitive assessment after 6 and 12 months. To mitigate this risk, we will make our best efforts to retain subjects through periodic follow up; and we will increase the number of recruited individuals at T0 to take into account an approximately 20% dropout rate. Although not all individuals may complete all follow-up sessions, the protocol will still provide valuable data that will allow us to investigate the muscular and neurophysiological correlates of AIS compared to CTRL at enrollment (T0). The forearm bisection task, block (iv), and resting-state EEG recording can still provide us significant information regarding possible body schema alterations, neurophysiological patterns, and postural performances.

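### The global test over T0, T1 and T2 uses only girls with all three visits, so a girl who leaves after T1 is dropped from it together with her recorded T1 data

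*Protocol article*

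**What the plan says.** Under Foreseen data processing, the article compares the two groups and looks for differences "between the three time points evaluation (T1, T0 and T2"). The pairwise tool is "A two-tailed paired sample t-test or a two-sided Wilcoxon rank sum test", applied "after having run a global test (either repeated measure ANOVA, or Friedman test depending on data normality").

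The visit schedule differs by group. Under Experimental design, the assessments "will be repeated after 6 (T1) and 12 months (T2) of therapy in AIS and after 12 months (T2) in CTRL". Controls therefore have no T1 visit.

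On numbers, Procedure says "We estimate recruiting 40 subjects", allows for 20% dropout (about 8 subjects) and expects 15 girls per group. The Discussion foresees that girls with scoliosis may miss the 6- and 12-month assessments. It answers with retention efforts, and "we will increase the number of recruited individuals at T0 to take into account an approximately 20% dropout rate". For girls who do not complete follow-up, it presents the T0 comparison with controls as still usable. It does not mention T1 results of girls who later miss T2.

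The 6-month change is a stated expectation. The Discussion expects body-schema alterations "which should improve significantly after the 6 month exercise and brace-treatment period (T1"), and it expects better body-image self-attitude scores at T1.

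**The concern.** Classical repeated-measures ANOVA and the Friedman test work on complete blocks. A subject with any visit missing contributes nothing, including the visits she attended. The article names these two tests and also foresees losses at 6 and 12 months, so some recorded T1 assessments may go unused in the test that precedes the pairwise comparisons.

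Two things are at stake. One is precision, in a group of about 20 girls. The other is selection: recruiting more girls replaces numbers, but it does not make those who stay resemble those who leave. If leaving is related to how a girl is doing at T1, a result from three-visit completers describes a selected group.

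**Working it through.** **Inputs from the article.** 40 recruited; 20% dropout; 30 evaluable (15 + 15); three visits for girls with scoliosis; two visits (T0, T2) for controls.

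**Assumptions.** An equal split, so 20 girls with scoliosis. The timing of dropout is not given, so it is varied. Outcome SD 1 at each visit, higher score worse, true T0–T1 change −0.50 SD, within-girl correlation ρ from 0.5 to 0.8.

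**1. The article's own figure.** 40 × 0.8 = 32, against 30 stated. In reverse, 30 / 0.8 = 37.5, so 38, against 40 stated. Both agree to within 2 subjects. The point does not rest on this figure.

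**2. Do the tests need complete blocks?** Both were run on 20 simulated girls with T2 missing for 4. The repeated-measures ANOVA routine stopped because the data were unbalanced, and the Friedman test returned no result. The 4 girls have to be removed whole, T1 included.

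**3. How many T1 assessments are discarded?** Three-visit completers: 20 × 0.8 = 16. T0–T1 pairs = 16 + number leaving after T1.

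| When the 4 girls leave | T0–T1 pairs recorded | Used by global test | T1 results discarded |
|---|---|---|---|
| All before T1 | 16 | 16 | 0 |
| Half before, half after | 18 | 16 | 2 (11%) |
| All after T1 | 20 | 16 | 4 (20%) |

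For a paired t-test (two-sided 5%, 80% power), the detectable change, in SDs of the within-girl difference, is 0.75 with 16 pairs, 0.70 with 18 and 0.66 with 20.

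**4. Bias if the completer set is also used for the T0–T1 contrast.** Let m be the mean standardised T1 score among those who stay. With equal SDs, the expected change among stayers is −0.50 + (1 − ρ) × m.

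- Worst fifth at T1 lost: m = −0.280 / 0.8 = −0.35.
- Loss of 20% with odds ratio 3 per SD of worse T1 score: m = −0.186.
- Loss of 20% with odds ratio 2 per SD: m = −0.129.

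| Loss after T1 | ρ = 0.5 | ρ = 0.6 | ρ = 0.8 |
|---|---|---|---|
| Odds ratio 2 | −0.56 | −0.55 | −0.53 |
| Odds ratio 3 | −0.59 | −0.57 | −0.54 |
| Worst fifth lost | −0.68 | −0.64 | −0.57 |

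Example: ρ = 0.6, worst fifth lost, −0.50 + 0.4 × (−0.35) = −0.64. If leaving is unrelated to the T1 score, m = 0 and the answer stays −0.50.

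**5. The alternative that the article permits.** In 20,000 simulated samples of 20 girls (ρ = 0.6, odds ratio 3, all loss after T1), completers gave −0.58, with SD 0.22 across samples. A plain paired difference on all T0–T1 pairs gave −0.50, with SD 0.20. The bias in step 4 comes from restricting to completers, not from the paired test.

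**The case against.** The tempting stronger reading is that the 6-month improvement will be estimated only in girls who stayed to T2. The article does not say this. The paired test identifies differences between visits; it needs only T0 and T1, and nothing limits it to girls with T2. The ANOVA or Friedman step only comes before it. This objection stands: the bias figures are conditional on a completer set that the article neither specifies nor excludes.

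A reader might also infer that girls with poor body image are the likely leavers, because the Introduction says altered body image is something "which has detrimental effects both on quality of life and adherence to treatment". That sentence concerns adherence to treatment, not attendance at research visits. The Discussion ties its own risks to boredom, duration, complexity and availability. Selective leaving is therefore possible but not established.

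Nor does the article rely on over-recruitment alone. It commits to periodic follow-up, allows the session to be split over three days, and allows the tasks to be simplified after the pilot recordings. These measures may reduce loss. They do not change what the named tests do with a missing T2. And only girls who leave after T1 have a T1 result to lose.

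Finally, a journal article may leave the handling of missing data to a fuller plan. That would answer a complaint about silence. Here the article names two tests that cannot use incomplete records, alongside a dropout it expects.

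**Conclusion.** The point holds in a limited form. As written, the global test excludes every girl without all three visits and discards 0 to 4 recorded T1 assessments out of 16 to 20. This assumes 20 girls with scoliosis and 20% dropout; the count depends on when they leave. By the same mechanism, a three-visit test cannot include any control, since controls have no T1 by design.

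An overstated 6-month change (−0.53 to −0.68 for a true −0.50 SD) follows only if three things hold together: the completer set is carried into the pairwise step, loss falls after T1, and leaving depends on the T1 score. The correlations and odds ratios behind that range are assumptions. With all T0–T1 pairs kept and all loss after T1, there is no such bias. The matter is worth correcting because the method is already named and the change is cheap, not because a biased result has been shown.

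**What to change.** - Replace the repeated-measures ANOVA or Friedman step with a linear mixed model on all recorded visits: visit as a factor and a random intercept per girl. Where controls are included, add group and group-by-visit terms; controls then contribute T0 and T2. Where normality fails, fit the model to transformed or ranked data.
- State that the T0–T1 contrast uses every girl with both T0 and T1, whether or not she attends T2.
- Compare the T0 scores of completers and leavers. These data are already recorded.

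The cost is a change of wording and slightly more analysis work, with no extra visits or measurements. The downside is that the mixed model assumes dropout is explained by the recorded data. If girls leave for reasons tied to what would have been seen later, some bias remains, and the comparison of completers with leavers can only hint at it.
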